### Study objectives (rationale and comparators)

This experimental study aims to investigate whether worry and rumination, two forms of RNT, share underlying cognitive mechanisms. We focus on negative interpretation bias, a transdiagnostic cognitive process prevalent in GAD and depression (see ref. 14) and shown to play a causal role in influencing levels of worry^17^ and rumination^19^ in single-session experimental studies. Using CBM-I, we investigate whether repeatedly training positive interpretations over multiple sessions (vs an active control condition) leads to a sustained reduction in worry and rumination in the disorders in which they play central maintaining roles, namely GAD and depression. Individuals with GAD or depression will receive worry-related or rumination-related training materials, respectively, to maximise potential training of interpretations relevant to the key form of RNT for the given disorder. We assess interpretation bias, levels of worry and rumination (primary outcomes) as well as anxiety and depression symptoms (secondary outcomes) at baseline (study visit 1) and again after multisession CBM-I or active control sessions (study visit 2). In addition, we examine the sustained impact of training positive interpretations on levels of worry, rumination, anxiety and depression at 1-month follow-up. Further, we compare two types of CBM-I, with and without prior RNT, to examine whether activating RNT modulates the effects of CBM-I in individuals with GAD and depression. Finally, to consider how cognitive processes may influence each other, and drawing on the combined cognitive bias hypothesis^36^ as well as building on findings that single-session CBM-I increases attentional control during worry,^18^ we include a classic Stroop and emotional Stroop task to examine whether multisession CBM-I impacts the ability to inhibit irrelevant and RNT-related information.

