#### Randomisation and blinding

Participants will be randomised to one of the three conditions on the basis of a random allocation sequence generated on http://www.random.org by a person not involved in the research study. As in Williams, Blackwell, Holmes and Andrews,^39^ numbers 1–3 corresponding to the three conditions will be placed in sealed envelopes, the envelopes marked with the ascending sequence order number, and participants allocated to conditions according to this sequence. Participants will remain blind to the condition until the end of the study (when they will be debriefed). Researchers will open the envelope at the first experimental session once participants have provided written informed consent. Blinding of the researchers will not be possible as researchers guide participants through the first online session, which differs by experimental condition (see below).

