### Procedure

Participants will be invited to take part in a research study into worry and rumination which includes two face-two-face study visits scheduled 3 weeks apart, nine homework sessions to be completed online between study visits and a follow-up questionnaire to be completed online 1 month after the second study visit (see figure 2 for participant flow through the components of the study). Prospective participants will be recruited from the community and from King's College London. They will complete an initial screening questionnaire online, including the PSWQ, RRS, PHQ-9 and GAD-7. If they meet inclusion criteria, the SCID will be completed by a trained researcher to confirm a diagnosis of GAD or depression. Once enrolled, participants will complete a presession questionnaire including standardised measures (PSWQ, RRS, PHQ-9, GAD-7, RNTQ) as well as demographic information online within 24 hours prior to the first study visit (experimental session). Should participants indicate risk to themselves (a score of >1 on PHQ-9 suicidal ideation item) on the preassessment questionnaire, this will trigger a risk assessment at the study visit.

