Up to 24 hours before returning for their second study visit, participants will again complete the presession questionnaire (PSWQ, RRS, PHQ-9, GAD-7, RNTQ), and additionally will complete a ‘negative events form’ in relation to the previous 3 weeks to assess incidence of mental health-related events (eg, deterioration in symptoms, suicidal intent, hospitalisation, etc). Any events reported will be addressed with the participant at the second study visit; events may also be captured during other points of the study and will be addressed with the participant when they are raised. If the event is related to an aspect of the study, an adverse events form will be generated, which will be reviewed by the Research Steering Committee. At the second study visit, participants will again provide written informed consent for this visit, will complete treatment expectancy and acceptability ratings, assimilation and imagination ratings (in reference to the past nine sessions), and will then complete the scrambled sentences test, classic and emotional Stroop task, recognition memory test and breathing focus task before being debriefed and partially paid for their participation to date. One month after their second study visit, participants will complete the follow-up questionnaire online, which is identical to the presession questionnaire for study visit 2, and receive the final payment for their participation. The experimenter will contact participants for further information should any negative events and/or mental health-related events be reported at follow-up. Participants will receive £130 for their participation in the study.

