### Statistical methods

Statistical analyses will be carried out in Stata V.14 (StataCorp. Stata Statistical Software: Release 14. 2015, College Station, Texas, USA: StataCorp LP) and MPlus.^62^ All variables will be described by diagnostic group, experimental condition and assessment time point. In addition, assessments of feasibility and acceptability in terms of recruitment, drop-out and rate of completion will be summarised, and additional measures relating to the experimental materials will be evaluated to check the manipulations worked as intended.

As this experimental study is designed to test hypotheses regarding the causal role of interpretation bias in worry and rumination in GAD and depression, analyses will be conducted using data from ‘completers’ only, defined as participants who complete ≥8/10 sessions (percentage judged to be an adequate ‘dose’ in previous multisession CBM-I studies^25^
^26^) and who return for the second study visit within 1 month of their first visit.

To consider differences between GAD and MDD diagnostic groups that received tailored training materials, we will specify multigroup models with diagnostic group as grouping variable. We will test whether parameters differ significantly between the two diagnostic groups. Further, we can examine significant effects within each diagnostic group. Predictors in each model are experimental condition (CBM_RNT, CBM_STAND, CONTROL) and time point (study visits 1, 2 and follow-up; follow-up for questionnaire measures only).

We will examine effects on measures of interpretation bias to assess whether the CBM-I conditions are successful in training positive interpretations (near transfer). We will then assess effects on measures of RNT (self-report and behavioural) as well as anxiety and depression to investigate the impact of our CBM-I conditions on changing RNT, anxiety and depressive symptoms (far transfer). Further, we will examine whether the extent of change on self-report measures of anxiety and depression falls within the range of reliable change, defined as a reduction in scores exceeding the reliable change index for that measure. We will supplement the above analyses with disorder-specific analyses, examining the effects on near transfer for disorder-specific items only (see the Interpretation bias measures). We will control for differences in demographic variables as appropriate by including them as covariates in analyses.

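### The protocol promises participant blinding until the end of the study but debriefs at visit 2, one month before the self-report follow-up; if that debrief discloses condition, the follow-up scales are unblinded

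*Protocol article*

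**What the plan says.** The Randomisation and blinding section gives the rule: "Participants will remain blind to the condition until the end of the study (when they will be debriefed". It adds that the researchers cannot be blinded.

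The Procedure section gives the order of events. At visit 2 participants give ratings and complete the behavioural and cognitive tasks, ending with the "breathing focus task before being debriefed and partially paid for their participation to date". Then: "One month after their second study visit, participants will complete the follow-up questionnaire online". The final payment follows that questionnaire.

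The opening of the Procedure section lists, among the components of the study, "a follow-up questionnaire to be completed online 1 month after the second study visit". Its content is given as one "which is identical to the presession questionnaire for study visit 2", and for that visit "participants will again complete the presession questionnaire (PSWQ, RRS, PHQ-9, GAD-7, RNTQ", together with a negative events form. The Statistical methods section confirms that no task is repeated at that point: "follow-up for questionnaire measures only".

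The objective that depends on this time point is in Study objectives: "we examine the sustained impact of training positive interpretations on levels of worry, rumination, anxiety and depression at 1-month follow-up".

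**The concern.** Two sections place debriefing at different times, and it is the event that ends participant blinding. If the Procedure section is followed and the debrief discloses condition, control participants learn that their scenarios were deliberately left unresolved, and CBM-I participants learn that they received the training, before the last outcome is collected.

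That outcome consists entirely of self-report scales, which are open to expectancy and disappointment. No behavioural or blind-coded measure is taken at one month to set against them. The researchers are already unblinded, so participant blinding is the main protection these scales have. The active control was designed to match CBM-I closely so that effects could be credited to changed interpretations, and disclosure would weaken that match for the follow-up. Expectancy is rated at visits 1 and 2, at visit 2 before the debrief, and no later rating is described that would show a shift.

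At stake is the claim of a sustained reduction in worry, rumination, anxiety and depression.

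**Working it through.** No sample-size or power figure of the plan enters this point, so there is none to reproduce. The check is of the order of events, followed by an illustration of scale.

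**Order of events**

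1. Visit 1: consent, randomisation, baseline tasks and first online session. The baseline questionnaires are completed within the 24 hours before.
2. About three weeks later: questionnaires up to 24 hours before visit 2, then ratings and tasks at visit 2, then debriefing and part payment.
3. One month after visit 2: follow-up questionnaire, then final payment.

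The Procedure section counts step 3 as part of the study, so visit 2 is not the end of the study. The blinding rule and the visit-2 debrief therefore cannot both be followed as written. The article describes no partial debriefing at visit 2 and no second debriefing after follow-up.

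**Which outcomes come after the debrief**

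- Primary measures: scrambled sentences test, recognition memory test, breathing focus task, PSWQ, RRS, RNTQ. Three of these six (PSWQ, RRS, RNTQ) are repeated at follow-up.
- Secondary measures at follow-up: PHQ-9 and GAD-7.
- So all 5 follow-up scales come after the debrief. All visit-2 outcomes, questionnaires and tasks alike, come before it.

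**Illustration of scale (assumed shifts, not estimates)**

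Take one unadjusted comparison of two conditions within a diagnostic group at the planned minimum of 20 per cell, with no true effect and a reporting shift of b SD caused by learning the condition.

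- SE = sqrt(2/20) = 0.316 SD.
- Two-sided type I error = P(Z > 1.96 − b/SE) + P(Z < −1.96 − b/SE).

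| Assumed b (SD) | b/SE | Type I error |
|---|---|---|
| 0 | 0 | 5% |
| 0.2 | 0.63 | 9.7% |
| 0.3 | 0.95 | 15.8% |
| 0.5 | 1.58 | 35.3% |

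A larger sample does not remove the bias. Pooling the diagnostic groups gives 40 v 40 and SE = sqrt(2/40) = 0.224, and a 0.3 SD shift then gives about 27%. The documents contain no figure for b.

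**How many could still be protected**

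The Protocol version and status section reports 59 participants complete at submission. The planned total is 60 + 60 = 120, so at most 120 − 59 = 61 remained, less anyone then between visit 2 and follow-up. Splitting follow-up by debrief timing would leave about 59/6 = 9.8 or 61/6 = 10.2 per cell across six cells, against the 16 per condition in the plan's own power calculation.

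**The case against.** The strongest objection is that the article does not say what the visit-2 debrief contains. This is a condensed account and the debrief script is not shown. The blinding section may be the governing rule, and the Procedure section may loosely describe closing a visit. This stands as a limit: a reader might infer that every follow-up outcome is certainly reported by unblinded participants, and the documents support that only conditionally. It does not remove the conflict, because the protocol itself ties the end of blinding to debriefing. Nor does reading the end of the study as visit 2 help: it would ease the wording, against the Procedure section's own list of components, but follow-up would still be unblinded.

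A second objection concerns scope, and it stands. The one-month assessment is presented as additional, and the sample size rests on the breathing focus task, which is not measured then. A reader might infer that the trial's main comparisons are compromised. They are not, since every visit-2 outcome is collected before the debrief. Nor does it follow that no follow-up difference could be credited to training: a difference already present under blinding at visit 2 and then maintained is much less vulnerable than one that first appears after disclosure.

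Third, the type I error figures rest on shifts that no passage supports and on a single unadjusted comparison, whereas the plan uses models over time points. They also concern CBM-I against control. For CBM-I with against without prior RNT, both arms receive positive training, so disappointment at having been a control does not apply. This too stands.

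**Conclusion.** The inconsistency is real and should be resolved. Its consequence is conditional: if the visit-2 debrief discloses condition, which is the natural reading of the blinding section, all five follow-up scales are unblinded, and a CBM-I versus control difference at one month could partly reflect expectancy or disappointment as well as training. That weakens the evidence for a sustained effect without voiding it.

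The damage is confined to the one-month time point; visit 1 to visit 2 comparisons stand. The size of any bias cannot be derived from the documents. The figures of 10%, 16% and 35% show what assumed shifts of 0.2, 0.3 and 0.5 SD would do at 20 v 20 and should not be read as the error rate of this trial.

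**What to change.** **Remaining participants.** Reconcile the Randomisation and blinding and Procedure sections by moving disclosure of condition and study purpose to after the follow-up questionnaire has been submitted. At visit 2 give only thanks, part payment and safety information.

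**Participants already debriefed.** The 59 complete at submission are the only number given; anyone then between visit 2 and follow-up would be in the same position. Record what was disclosed and when, report their follow-up data as unblinded where condition was revealed, and state this as a limitation.

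**Analysis and reporting.** Report the visit 1 to visit 2 contrasts separately from those involving follow-up, and interpret follow-up against the blinded visit-2 result. Treat any comparison by debrief timing as descriptive only: it leaves about 10 per cell and confounds timing with calendar period.

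**Cost.** For remaining participants, a changed visit-2 script and a debrief sheet sent online; the online follow-up and the final payment already come after visit 2, so no visit is added. For those already debriefed the change cannot restore blinding, and the cost is an acknowledged limitation on their follow-up data.

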### Monitoring adverse events

Adverse events (significant and prolonged increases in anxiety and/or depressive symptoms related to taking part in the study) will be recorded and reported to the Research Steering Committee at the end of the study. Serious adverse events (potentially life-threatening events, eg, suicide attempt, hospitalisation due to mental health, death, related to taking part in the study) will be reported immediately to the Chair and Deputy Chair of the Research Steering Committee. In addition, we will record other negative life events reported by participants.

### Data entry, coding, security and storage

The research will be conducted in compliance with data management and sharing policies set out by the Institute of Psychiatry, Psychology and Neuroscience, King's College London, and Nature Life Sciences reproducibility guidelines. Clinical data (eg, questionnaires; SCID forms) will be managed according to Mental Health Research Network (MHRN) guidance. All research data will be coded and anonymised and stored securely in accordance with the Data Protection Act 1998.

### Statistical methods

Statistical analyses will be carried out in Stata V.14 (StataCorp. Stata Statistical Software: Release 14. 2015, College Station, Texas, USA: StataCorp LP) and MPlus.^62^ All variables will be described by diagnostic group, experimental condition and assessment time point. In addition, assessments of feasibility and acceptability in terms of recruitment, drop-out and rate of completion will be summarised, and additional measures relating to the experimental materials will be evaluated to check the manipulations worked as intended.

As this experimental study is designed to test hypotheses regarding the causal role of interpretation bias in worry and rumination in GAD and depression, analyses will be conducted using data from ‘completers’ only, defined as participants who complete ≥8/10 sessions (percentage judged to be an adequate ‘dose’ in previous multisession CBM-I studies^25^
^26^) and who return for the second study visit within 1 month of their first visit.

To consider differences between GAD and MDD diagnostic groups that received tailored training materials, we will specify multigroup models with diagnostic group as grouping variable. We will test whether parameters differ significantly between the two diagnostic groups. Further, we can examine significant effects within each diagnostic group. Predictors in each model are experimental condition (CBM_RNT, CBM_STAND, CONTROL) and time point (study visits 1, 2 and follow-up; follow-up for questionnaire measures only).

We will examine effects on measures of interpretation bias to assess whether the CBM-I conditions are successful in training positive interpretations (near transfer). We will then assess effects on measures of RNT (self-report and behavioural) as well as anxiety and depression to investigate the impact of our CBM-I conditions on changing RNT, anxiety and depressive symptoms (far transfer). Further, we will examine whether the extent of change on self-report measures of anxiety and depression falls within the range of reliable change, defined as a reduction in scores exceeding the reliable change index for that measure. We will supplement the above analyses with disorder-specific analyses, examining the effects on near transfer for disorder-specific items only (see the Interpretation bias measures). We will control for differences in demographic variables as appropriate by including them as covariates in analyses.

To examine the mediating role of interpretation bias, we will conduct mediation analyses using Baron and Kenny's^63^ approach. Depending on the final sample size and distribution of the data, bootstrapped SEs and bootstrapped CIs will be estimated.

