#### Sample size

Prior single-session CBM-I research with participants with GAD has indicated that CBM-I training (vs control) had a large effect on the breathing focus thinking task (*f^2^*=0.43,^17^ see below for task description). Using G*POWER software^41^ to calculate sample sizes achieving 80% power at p=0.05, N=49 in each group (16 per condition) would be needed to reveal a large effect size on the breathing focus task. We based our power calculation on this far transfer task because far-transfer is more difficult to achieve than near transfer, and near-transfer effects of multisession CBM-I training have been found to be large (see ref. 42). Based on this calculation, we aim for a final cell size of at least n=20 participants per condition in each diagnostic group.

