**Figure 2 BMJOPEN2016013404F2:**

Participant flow chart with measurement points.

At the first study visit (experimental session), participants provide written informed consent and will be randomised by diagnostic group to one of the three conditions: (1) CBM_RNT, (2) CBM_STAND or (3) CONTROL (see the Experimental conditions section above for details). They will then complete the scrambled sentences test, classic and emotional Stroop task, recognition memory test and breathing focus task. Then, participants will be given the study rationale for the online homework sessions and will complete expectancy and acceptability ratings before completing the first online session on the study website. This is completed during the study visit to ensure participants understand the instructions for their condition and are able to complete the sessions correctly. Each session includes the RNT induction (CBM_RNT) or neutral task (CBM_STAND and CONTROL conditions), followed by 50 scenario audio clips (see above) with a short break after 25 scenarios. In addition, participants complete ratings of state levels of worry, rumination, anxiety and depression after the prescenario task (RNT or neutral task) and at the end of each session. Following the first online session, participants complete the recognition memory test again (different scenarios; see above) to assess change from pre to post first study visit. Finally, participants are presented with instructions for completing the nine online sessions over the course of the next 3 weeks, and the researcher will complete a diary card with each participant to help schedule the homework sessions.

Participants will complete three online sessions per week over the next 3 weeks, with some flexibility in terms of dates and times of day, and with the provisos that they complete no more than one homework session per day and complete the homework sessions within 1 month and the final session no later than the day before their second study visit. Researchers will monitor adherence to the homework sessions using the online platform. They will keep in touch with participants by using participants' preferred method of contact (email, phone, SMS) to facilitate engagement and trouble shoot issues with the online sessions, and will encourage participants to catch up missed sessions. Participants are required to complete a minimum of eight sessions (see also the Statistical methods section).

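### The outcome model treats the visit-1 score as an outcome and states no baseline adjustment, giving up precision that the collected baseline scores could supply at almost no cost

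*Protocol article*

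**What the plan says.** The Statistical methods section sets out the outcome model in three steps.

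- Diagnostic group enters as the grouping variable: "we will specify multigroup models with diagnostic group as grouping variable". Effects may also be examined within each diagnostic group.
- The model terms named are condition and time: "Predictors in each model are experimental condition (CBM_RNT, CBM_STAND, CONTROL) and time point (study visits 1, 2 and follow-up". The third time point applies to questionnaires only.
- The only covariates named are demographic: "We will control for differences in demographic variables as appropriate by including them as covariates in analyses".

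The Study objectives section makes visit 1 the baseline, with outcomes assessed "at baseline (study visit 1) and again after multisession CBM-I or active control sessions (study visit 2". The baseline values are collected before training. The Procedure section says that, within 24 hours before the first visit, "participants will complete a presession questionnaire including standardised measures (PSWQ, RRS, PHQ-9, GAD-7, RNTQ". For the tasks, given at visit 1 ahead of the first online session, it says "They will then complete the scrambled sentences test, classic and emotional Stroop task, recognition memory test and breathing focus task".

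No baseline score is named as a covariate, and equal visit-1 means across conditions are not stated.

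**The concern.** With visit 1 as one level of time and its means left free in each condition, the treatment effect is the difference between conditions in change from visit 1. That contrast subtracts the whole baseline score, whatever its correlation with the later score, and so carries the baseline noise along with it. Regression on the baseline score uses only as much of it as predicts the outcome. The target is 20 completers per condition in each diagnostic group, and effects are examined within diagnostic groups, so precision per contrast matters.

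The covariate sentence does not supply this precision. It names demographics only, gives no list, and ties inclusion to differences and to a judgement of what is appropriate. If it is applied to the randomised conditions, the choice can be made after the data are seen. With complete visit 1 and visit 2 data, a demographic main effect is also the same at both visits, so it cancels from the condition-by-time contrast.

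**Working it through.** **Inputs from the protocol article.** Condition and time are the predictors, and visit 1 is both a time level and the baseline (Statistical methods; Study objectives). The target is n=20 per condition in each diagnostic group, 60 per group (Sample size). Alpha is 0.05; sidedness is not stated and two-sided is used here.

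**Inputs not in the document (assumptions).** The baseline-to-post correlation r, shown from 0.3 to 0.8; a standardised effect d=0.8, varied below; and equal variances at the two visits.

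**The plan's own figure.** The Sample size section reports that "CBM-I training (vs control) had a large effect on the breathing focus thinking task (*f^2^*=0.43" and derives 49 per diagnostic group for a design "achieving 80% power at p=0.05". A one-way ANOVA with three conditions needs 26 in total if f²=0.43, or 56 if 0.43 is read as f. A total of 49 is reached only with inputs that are not stated. One example is a between-factor repeated-measures test with f=0.40, three groups, two measurements and r=0.5. The derivation is therefore under-specified rather than shown to be wrong. It gives no value of r to use here.

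**Variance of one CBM-I versus CONTROL contrast, in units of SD².**

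- Change from visit 1 (condition-by-time, free baseline means): 2(1−r) × 2/n
- Baseline-adjusted: (1−r²) × 2/n
- Ratio, adjusted to change: (1−r²) / [2(1−r)] = (1+r)/2

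For n=20 and r=0.5, change gives 2 × 0.5 × 0.1 = 0.100, adjusted gives 0.75 × 0.1 = 0.075, and the ratio is 0.75.

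**Results.** Power is from the noncentral t distribution with n=20 per arm and d=0.8 (38 degrees of freedom for change, 37 for adjusted).

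| r | Variance ratio | Reduction | Power, change | Power, adjusted | Adjusted N matching 60 under change |
|---|---|---|---|---|---|
| 0.3 | 0.65 | 35% | 55% | 73% | 39 |
| 0.5 | 0.75 | 25% | 69% | 81% | 45 |
| 0.7 | 0.85 | 15% | 89% | 93% | 51 |
| 0.8 | 0.90 | 10% | 97% | 98% | 54 |

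The last column is 60 × (1+r)/2. At r=0.5 the change contrast has the same power as ignoring baseline altogether (69%); below that it has less.

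**Simulation check.** In 4,000 simulated trials at each of r=0.3, 0.5 and 0.7, the variance ratios were 0.66, 0.76 and 0.86. Both estimators averaged about −0.80 for a true effect of −0.80, so the difference is one of precision and not of bias.

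**Sensitivity to the effect size.**

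- f²=0.43 taken literally as a two-group effect: d = 2√0.43 ≈ 1.31. At r=0.5, power goes from 98% to over 99%.
- 0.43 read as f: d ≈ 0.86. At r=0.5, power goes from 76% to 86%; at r=0.7, from 93% to 96%.

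**The case against.** The strongest reply is that nothing here is an error. Under randomisation both contrasts estimate the same effect. The protocol article is condensed, and a longitudinal model could impose equal visit-1 means without the article saying so. The gain depends on two quantities that the document does not give, and it nearly vanishes at high r or at the cited effect size taken literally. All of that stands, and it limits the point to an improvement in precision of uncertain size. It does not remove the point, because the article does set out the predictors and covariates for each model, and the baseline score has no stated role beyond being an outcome.

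Two stronger readings are tempting, and the document supports neither.

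- A reader might infer a model with main effects only, in which the condition term averages visit 1 with visit 2 and so halves the effect. The Design and Statistical methods sections frame the aim as change in the outcomes, which implies condition-by-time. A condensed article need not spell out the interaction.
- A reader might infer that the covariate sentence is a test of whether randomisation worked. It mentions no imbalance test and does not say between which groups demographics might differ. GAD and MDD are not randomised groups, and demographic adjustment of that comparison is legitimate.

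**Conclusion.** The point holds as a matter of efficiency. As described, and with free visit-1 means, the analysis is a change-score comparison. Adjusting for the baseline score gives a smaller variance for any r below 1, apart from the single degree of freedom spent. Under the assumed d=0.8 with 20 per arm, the gain in power is about 18 percentage points at r=0.3, 12 at r=0.5, 4 at r=0.7 and 1 at r=0.8. It is small at any of these r if the effect is near d=1.31: at most about 6 points, at r=0.3 (93% to 99%).

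Lack of bias rests on randomisation. The analysis set is completers, selected after randomisation, so equal baseline means are not assured in the set analysed. Neither contrast repairs that selection, but it is a reason to prefer a covariate to an equal-means constraint.

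On demographic covariates the conclusion is narrower. For comparisons between randomised conditions, the wording leaves room to choose after seeing the data. It does not show that this was intended.

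**What to change.** Replace the predictor and covariate wording in Statistical methods with a paragraph that states the following.

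1. Within each diagnostic group, visit 2 (and follow-up for questionnaires) is modelled with the pre-training visit-1 score of the same measure as covariate. The condition effect is reported at each post-baseline time.
2. The baseline is defined where a measure is taken more than once at visit 1. For the recognition memory test, use the administration before the first online session, not the one after it. For the breathing focus task, use the matching phase (before or after the worry or rumination period).
3. The covariate is used in preference to constraining visit-1 means to be equal, because the analysis set is completers.
4. For comparisons between randomised conditions, any demographic covariates are named on prognostic grounds before the outcome data are analysed by condition, and not chosen from observed differences. Unblinding is not a usable cut-off, since the researchers know the allocation from the first visit.

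The cost is one degree of freedom per model and a paragraph of wording. No new data and no design change are needed.
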